**Discussion:**

This is a phase III trial to evaluate the safety and efficacy of wound infusion with steroid and local anesthetic. The study is aimed also to evaluate how long this infusion has to be maintained in order to maximize effectiveness. Our data are intended to quantify the amount of ropivacaine and methylprednisolone needed by patients undergoing major abdominal surgery, to be stored in a new nanotechnology device for sustained pain treatment after surgery. We also aim to clarify the roles of inflammatory response, oxidative stress, and genetic background on postoperative and persistent pain after major abdominal surgery.

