### Procedures - clinical study

On the day of surgery, patients come to the operating room and are provided with standard monitoring (electrocardiogram, oxygen saturation, non-invasive blood pressure, and invasive pressure monitoring). General anesthesia is given using propofol and midazolam (as deemed appropriate by the anesthesiologist), opioids (fentanyl 0.2 μg/kg or remifentanil 0.1-0.25 mg/kg per min or both), and muscle relaxants (cisatracurium/rocuronium) and maintained with sevoflurane.

A morphine bolus of 0.15 mg/kg is given 30 to 45 min before the end of surgery. An infusion catheter (Baxter Painfusor®; Baxter International, Deerfield, IL, USA) is placed by the surgeon in the fascial plane between peritoneum and fascia trasversalis, and a 10-ml bolus of 0.2 % ropivacaine is administered immediately after muscular plane closure; the catheter is then connected to an electronic pump (CADD®-Solis; Smiths Medical, Dublin, OH, USA) to give a continuous infusion of pain medications.

During the first 24 h, all patients receive ropivacaine 0.2 % + methylprednisolone 1 mg/kg, 10 ml/h (total volume of 240 ml in 24 h) continuous wound infusion; additionally, either acetaminophen 1000 mg or ketorolac 30 mg every 8 h is prescribed.

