### After 24 h, patients are randomly assigned between two groups of treatment:

Treatment group: 10 ml/h continuous infusion of ropivacaine 0.2 % + methylprednisolone 1 mg/kgPlacebo group: 10 ml/h continuous infusion of saline 0.9 %.

Regardless of treatment group, rescue analgesia in the first 48 h is provided by PCA pump with morphine (0.5 mg/ml, bolus 1 mg, lock-out 5 min, 20 mg limit every 4 h).

Random group allocation of patients is made through a computer-generated sequence. To maintain blinding, a research fellow who is not taking part in patient evaluation is in charge of preparing and programming all of the pumps used during the study: an opaque, sealed, sequentially numbered envelope is assigned to each patient and is opened by the same research fellow after the first 24 h of treatment.

Patients and their anesthesiologists are blind to treatment assignment. A clinical resident, who is not involved with randomization, is in charge of all clinical evaluations as part of the daily clinical practice.

The envelope is maintained apart from the patient’s case report form and is to be opened in every potentially harmful situation for the patient but only when care providers need to be aware of the patient’s treatment. All ropivacaine and methylprednisolone vials used during the study are registered with their code in order to be tracked and recognized in the future for any issue potentially hindering the validity of data.

At 48 h, morphine PCA is removed, and all patients are treated with Patient-Controlled Intrawound Analgesia (PCA through the wound catheter) with either ropivacaine 0.2 % alone or saline according to the group of randomization up to a maximum of 7 days after surgery. The catheter is removed at the seventh postoperative day or after 36 h of non-use (no self-administered bolus). After PCA removal, rescue additional analgesia is provided by tramadol (100 mg or 50 mg according to patient’s weight of not more than or of more than 50 kg).

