We decided to analyze both local and systemic inflammatory response for the following reasons. First, systemic inflammation is advocated to be a risk factor for postoperative and persistent pain [5], but few data exist, and failed in the identification of standard values of inflammatory markers as predictors of pain; therefore, we guess our data could configure as a reference for future studies. Second, we want to investigate whether local and systemic cytokine expressions are linked or not, and how. Third, we aim to investigate the effect of a peripheral block on systemic inflammation because previous studies have provided an incomplete understanding [11]. Furthermore, there is evidence of the role of free radicals as a crucial mediator of pain of different etiologies [31–33], and we will also investigate the free-radical formation and correlate these data to the inflammatory response.

The maintenance of CWI up to 7 days could also be questioned because we traditionally consider the first 48 h after surgery to be the most challenging and to be associated with the highest pain values, and most of the studies consider a 2-day infusion after surgery; otherwise, studies on incisional pain have demonstrated that sensitization processes tend to restart after suspension of analgesia [34]. Therefore, an effective nociceptive block should cover the entire perioperative period, aiming to fight pain until it lasts. Use of patient-controlled wound infusion arguably allows prolongation of the analgesic infusion as deemed necessary by the patient, without drug overdosing, and will help quantify the average amount of drugs needed in the first 7 days after major abdominal surgery. This final issue is to be considered carefully because our study is part of a wider one aimed to validate a new nanotech device for pain treatment: this device is being created by bio-engineers and will be tested for bio-compatibility in rats. The final aim is to develop a new analgesic tool to be based on nanotechnology and to be applied on the surgical wound in humans for sustained release of pain medications and growth factors after surgery and to be finally re-absorbed by tissues. In this perspective, our study is the first step of a longer project and is focused on investigating (1) the efficacy and safety of topical methylprednisolone, (2) the average dose of pain medications required in the perioperative period, and (3) the average needed duration of a wound infusion.

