With this study, we aim to validate the use of methylprednisolone for CWI to reduce morphine consumption and associated side effects as well as PPSP after abdominal surgery. Moreover, we want to investigate whether genetic polymorphisms might be biomarkers for postoperative pain and opioid consumption. These results should be used to define delivery times and dosages for the new nanotechnology platform we are currently developing for sustained postoperative pain relief to be used in clinical practice and should be able to improve perioperative and long-term outcome for patients.

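### The amount of drug needed over 7 days cannot be learned from patient demand before 48 h, nor for methylprednisolone at any time; only later ropivacaine bolus use is demand-driven, and it needs the saline arm, pain and rescue beside it

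*Protocol article*

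**What the plan says.** The article gives the trial a dose-quantifying purpose in three places.

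- Abstract, Discussion: "Our data are intended to quantify the amount of ropivacaine and methylprednisolone needed by patients", with a view to loading a sustained-release device.
- Main Discussion: patient-controlled wound infusion "will help quantify the average amount of drugs needed in the first 7 days after major abdominal surgery". The second of three listed aims is "the average dose of pain medications required in the perioperative period".
- End of the main Discussion: "These results should be used to define delivery times and dosages for the new nanotechnology platform".

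The delivery schedule is as follows.

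- Procedures - clinical study: "a 10-ml bolus of 0.2 % ropivacaine is administered immediately after muscular plane closure". Every patient then has a continuous 10 ml/h infusion of ropivacaine 0.2 % with methylprednisolone 1 mg/kg for 24 h, stated as 240 ml in total.
- The section on random assignment after 24 h: "Treatment group: 10 ml/h continuous infusion of ropivacaine 0.2" %, again with methylprednisolone 1 mg/kg. The placebo group has saline at the same rate.
- From 48 h, both groups give themselves boluses through the wound catheter, "with either ropivacaine 0.2 % alone or saline according to the group of randomization". The catheter comes out on day 7, or earlier after 36 h without a bolus.
- Abstract, Methods/Design: each bolus is 10 ml, at most one per hour, capped at 40 ml per 4 h.

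Study outcomes and Statistics neither define the amount needed nor name wound-bolus use as an outcome. Statistics does give a general between-group test for quantitative variables.

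**The concern.** An amount needed can be learned from patient control only where patients control delivery. The article claims such a quantity for the whole 7 days and for both drugs, but its own schedule puts neither drug under patient control before 48 h and never does so for the steroid.

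After 48 h there is a second difficulty. Placebo patients have the same button and receive saline, so presses also occur without active drug. Bolus volume in the ropivacaine group taken alone measures use; whether that use reflects need for the drug is a further step. The Discussion itself allows that infused fluid might act by washing out cytokines, which is another reason to keep the saline group in view.

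At stake is the interpretation of a declared output: figures meant to inform the delivery times and dosages of a device. The primary comparison of morphine equivalents is not affected.

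**Working it through.** **Inputs (all from the article).** Ropivacaine 0.2 %, that is 2 mg/ml; closure bolus 10 ml; infusion rate 10 ml/h; on-demand bolus 10 ml with a 1 h lock-out and a 40 ml per 4 h cap; patient-controlled phase from 48 h to day 7.

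**1. The article's own figure.** 10 ml/h × 24 h = 240 ml. This matches the stated first-day volume.

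**2. Amount fixed by protocol, assuming the infusion runs to plan.**

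- Closure bolus: 10 ml × 2 mg/ml = 20 mg (both groups).
- 0 to 24 h: 240 ml × 2 mg/ml = 480 mg (both groups).
- 24 to 48 h: 240 ml × 2 mg/ml = 480 mg (treatment), 0 mg (placebo).
- Total to 48 h: 20 + 480 + 480 = 980 mg (treatment); 20 + 480 = 500 mg (placebo).

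These totals are the same whatever patients feel or ask for.

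**3. Amount open to patient demand.** Day 7 is 168 h, so the phase lasts 168 − 48 = 120 h. At one bolus per hour the ceiling is 120 boluses × 20 mg = 2400 mg (1200 ml). The 40 ml per 4 h cap gives the same ceiling. This is a pump limit and not an expected value; removal after 36 h of non-use will shorten the phase for some patients.

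**4. Fixed share of a 7-day total.** With b boluses after 48 h, the treatment-group total is 980 + 20b mg. The article gives no value for b, so the table covers an assumed range.

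| b (assumed) | Total, mg | Demand-driven, mg | Fixed share |
|---|---|---|---|
| 0 | 980 | 0 | 100 % |
| 10 | 1180 | 200 | 83 % |
| 40 | 1780 | 800 | 55 % |
| 120 | 3380 | 2400 | 29 % |

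If a 7-day total were used, it could not fall below 980 mg, and at low or moderate button use most of it would be set by protocol.

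**5. Methylprednisolone.** It appears in the 0 to 24 h infusion (all patients) and the 24 to 48 h infusion (treatment group), each at a fixed weight-based amount and a fixed rate. From 48 h the wound solution is ropivacaine alone or saline. The demand-driven part is therefore zero, and no patient-demand estimate of the steroid amount needed can be formed.

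**6. What the later bolus difference can show.** An effective drug may lower presses because pain is relieved, or raise them because pressing is rewarded. The ropivacaine-minus-saline difference thus has no clear sign as a measure of need. The groups also differed in both ropivacaine and steroid from 24 to 48 h, so the difference reflects the whole randomised regimen and does not isolate ropivacaine.

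**The case against.** The strongest reply has four parts.

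*No rule is stated.* A reader might infer that need will be computed as the average amount delivered, so that an inert drug would still yield a large requirement. The documents do not support this. No estimator is given, and the Discussion sentence credits patient-controlled use, which points to the phase after 48 h. A large figure is certain only if someone adds in the fixed 980 mg. This part stands.

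*The saline contrast is available.* A reader might also infer that ropivacaine use will not be set against saline use. That is silence in a condensed article. The concurrent saline group exists, pain and analgesic consumption are recorded, and Statistics has a general between-group test. This stands too, so the missing comparison is not in itself an error.

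*Equal pressing would not prove absence of need.* It could coexist with lower pain or less rescue. This is correct, and it is why bolus volume must be read together with those outcomes.

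*Efficacy is tested elsewhere, and device dosing is only rationale for a later project.* The primary endpoint would guard against carrying forward a regimen with no effect. But it pools 7 days and tests the combined regimen. A positive result could arise from 24 to 48 h or from the steroid, and would not show that later boluses met a need for drug. Nor does it give patients any control over delivery before 48 h or over the steroid at any time.

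What survives is a conflict between a stated claim and the stated schedule, which no unseen analysis detail would remove.

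**Conclusion.** The point holds as a limit on what the design can conclude. The article says that the data will quantify the ropivacaine and methylprednisolone needed over the first 7 days. By its own schedule, patient demand can inform only ropivacaine bolus use from 48 h to day 7. The first 980 mg of ropivacaine in the treatment group (if the infusion runs to plan) and all of the methylprednisolone are fixed exposure. The demand-driven part lies between 0 and 2400 mg by the pump limits; its likely value is not given.

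The documents do not show that a wrong formula will be used, that the saline group will be ignored, or that the trial must report a large requirement for an ineffective drug. The primary analysis is untouched; what needs correcting is the dosing claim and how bolus use will be presented.

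**What to change.** 1. In the Abstract's Discussion and at each place in the main Discussion where drug requirement or device dosing is mentioned, state that amounts given before 48 h, including all methylprednisolone, are fixed exposure and do not estimate need. Limit any demand-based estimate to ropivacaine bolus use after 48 h.
2. Report self-administered wound-bolus volume from 48 h to day 7 by day and by randomised group, with the between-group difference and 95% CI, beside pain scores and rescue use on the same days.
3. Call the treatment-group mean the amount used. Interpret it together with pain and rescue, and say that the bolus difference reflects the whole randomised regimen, including the earlier steroid.

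The cost is revised wording and one table. The saline group, pain scores and consumption records already exist; pump bolus counts should be kept, because the article does not name them separately. The trial was still enrolling, with 46 patients recruited when the article was written, so this could be set before analysis. No treatment rule changes. The downside is a more cautious dosing claim for the device.

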## Abstract

**Background:**

Inflammatory response is one of the key components of pain perception. Continuous infusion (CWI) of local anesthetics has been shown to be effective in controlling pain and reducing postoperative morphine consumption, but the effect of adding a potent anti-inflammatory drug (such as a steroid) has never been addressed. In our study, we want to investigate the effect of CWI with local anesthetic + methylprednisolone on acute and persistent pain, correlating clinical data with biomarkers of inflammation and genetic background.

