### Study outcomes

The primary outcome of the study is to investigate whether a wound infusion of local anesthetic and steroid has a higher analgesic efficacy compared with placebo during 7 days following surgery, assessed as analgesic consumption: the primary endpoint will be the reduction of morphine equivalents required in the first 7 days after surgery.

Secondary outcomes will include the differences in analgesia and side effects within 7 days after surgery. We will investigate any difference in pain at rest and movement (i.e., coughing and deep inspiration) by Numeric Rating Scale (11-point scale from 0 = no pain to 10 = worst imaginable pain), additional analgesic consumption, side effects (postoperative nausea and vomiting, sedation, and any signs of local anesthetic or steroid systemic toxicity), and incidence of persistent post-surgical pain. Differences in terms of wound healing or wound infections will be also assessed up to 3 months to assess any local side effect of steroid infusion. The degree of inflammatory response/oxidative stress between groups will be assessed to analyze the effect of CWI with either treatment or placebo. We plan to analyze the combined effect of some polymorphisms (by using a gene-candidate approach) of genes related to the development of PPSP, pain sensitivity, opioid response, and inflammatory reaction.

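### The two arms never differ in methylprednisolone alone, so the article's claims about the steroid's own efficacy and the amount needed cannot be tested in this trial

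*Protocol article*

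**What the plan says.** Treatment is set out in two places in the Methods. Under Procedures - clinical study: "During the first 24 h, all patients receive ropivacaine 0.2 % + methylprednisolone 1 mg/kg, 10 ml/h". Under the next heading, which describes randomization after 24 h, the treatment group continues ropivacaine with methylprednisolone at the same rate, and the placebo group receives "10 ml/h continuous infusion of saline 0.9" %. At 48 h both groups change to patient-controlled boluses into the wound, "with either ropivacaine 0.2 % alone or saline according to the group of randomization up to a maximum of 7 days after surgery".

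Study outcomes words the primary question for the combination: "whether a wound infusion of local anesthetic and steroid has a higher analgesic efficacy compared with placebo during 7 days following surgery".

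Three statements go further and concern the steroid itself:

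- Abstract, Discussion: "Our data are intended to quantify the amount of ropivacaine and methylprednisolone needed by patients".
- Discussion, on the purpose of the wider project: one focus is "the efficacy and safety of topical methylprednisolone".
- Discussion, closing paragraph: "we aim to validate the use of methylprednisolone for CWI to reduce morphine consumption and associated side effects as well as PPSP". The same paragraph says the results should set delivery times and dosages for the planned nanotechnology device.

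**The concern.** Whenever the arms differ in steroid, they also differ in local anesthetic. A lower morphine requirement in the treatment arm is therefore evidence about the combined regimen and says nothing separately about methylprednisolone. Yet the article announces conclusions about methylprednisolone alone and about how much of it patients need.

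This matters because of the use planned for the results. A positive trial, read against the closing paragraph of the Discussion, could be taken as support for putting a steroid, in some amount, into a device for human use. The trial would have shown only that continuing the combined infusion after 24 h does better than stopping it.

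**Working it through.** **1. The arms, period by period** (Methods, the two sections cited above)

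| Period | Treatment arm | Placebo arm | Arms differ in |
|---|---|---|---|
| 0–24 h | ropivacaine + methylprednisolone | the same | nothing |
| 24–48 h | ropivacaine + methylprednisolone | saline | both drugs together |
| 48 h to day 7, or earlier catheter removal | patient-controlled ropivacaine | patient-controlled saline | ropivacaine only |

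**2. What the randomized difference contains.** Let R be the effect on 7-day morphine equivalents of ropivacaine given after 24 h. Let M be the effect of the second 24 h of methylprednisolone, including any carry-over past 48 h. Let I be their interaction. The trial estimates one quantity,

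D = R + M + I.

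One equation cannot yield M. No row of the table sets M apart, because no arm receives ropivacaine without steroid between 24 and 48 h. More patients would make D more precise but would not separate M from it.

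**3. The plan's own effect size.** The Statistics section assumes a 50 % reduction and supports it with an audit and literature showing 30–50 % with local anesthetic wound infusion. Subtracting one from the other:

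- lower bound for the steroid's share: 50 − 50 = 0 points of the control mean;
- upper bound: 50 − 30 = 20 points.

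Much or all of the planned effect could therefore arise with no steroid effect.

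**4. The stated sample size.** The 50 patients per group cannot be reproduced because the article gives no SD or control mean. Working back for a two-sided 5 % test (sidedness is not stated, so this is an assumption) at 80 % power:

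- standardized difference = (1.960 + 0.842) × √(2/50) = 0.560;
- implied SD/control mean = 0.50/0.560 = 0.892.

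The identification argument does not depend on this ratio. It serves only to show the scale of a comparison in which the steroid alone differed. With equal SDs, the number per arm to detect 20 points would be

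n = 2 × (1.960 + 0.842)² × (0.892/0.20)² ≈ 313.

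Power for 20 points would be 20 % with 50 per arm and 23 % with 60 per arm. Over an assumed SD/mean range of 0.5 to 1.0, n runs from 99 to 393 per arm.

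**5. The amount of steroid needed.** Estimating a requirement needs either several dose levels or patient-titrated use. Methylprednisolone appears at one fixed weight-based amount, and after 48 h the self-administered solution contains no steroid. Bolus counts therefore measure demand for ropivacaine only.

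**The case against.** The strongest reply is that the tested hypothesis is already correctly framed. Study outcomes and Statistics both name the combination, and combination against placebo is a legitimate comparison. The closing sentence of the Discussion can be read as validating methylprednisolone within the combined infusion. This stands in part: the primary outcome is not undermined, and the problem is confined to statements in the Abstract and Discussion. It does not rescue the stated interest in the efficacy of topical methylprednisolone or in the amount required, because those name the steroid itself.

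The Discussion also offers two safeguards. The first is a check for a difference in morphine use at 24 h. That examines balance before the arms diverge and cannot separate two drugs withdrawn together. The second is the cytokine work, intended to distinguish steroid action from dilution by the infused fluid. Saline at the same rate does match volume from 24 to 48 h. But ropivacaine is not among the explanations considered, and the substudy (15 per group, 30 in all) uses the same two arms.

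Several stronger readings are tempting, but the documents do not support them:

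- *The steroid's share is zero.* It is unidentified. The plan's own range gives 0 to 20 points.
- *A fully positive result is exactly what ropivacaine alone would give.* That matches only the top of the 30–50 % range. The article does not say that those data concern stopping versus continuing after 24 h of active infusion, so they cannot be carried over directly as the expected ropivacaine effect here.
- *The steroid accounts for only 17 % of the contrast*, because the arms differ in it for 24 of 144 post-randomization hours. Hours are not morphine equivalents, and the Discussion itself notes that the first 48 h are traditionally associated with the highest pain values.
- *Ropivacaine is available throughout.* The catheter comes out after 36 h without a bolus, so access can end before day 7.
- *The Abstract states an aim to measure the effect of adding a steroid.* The remark that "the effect of adding a potent anti-inflammatory drug (such as a steroid) has never been addressed" describes a gap in the literature. The aim that follows names local anesthetic plus methylprednisolone.

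**Conclusion.** The point holds for the steroid-specific statements in the Abstract and Discussion, and only for those. The contribution of methylprednisolone to any difference in analgesic consumption or persistent pain is not identifiable, and its required amount is not estimable. This follows from the arm structure and needs no assumption about variability.

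The figure of 0 to 20 points of the control mean illustrates how much room the plan's own numbers leave. It assumes that the 30–50 % quoted for local anesthetic infusion applies to this comparison, which the article does not establish. The per-arm figures further assume the back-calculated SD/mean ratio and equal SDs.

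The primary comparison remains valid as continuing versus stopping. It is wrong to infer either that the steroid does nothing or that the trial fails its main question.

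**What to change.** Keep the primary outcome. Add one sentence saying what it estimates: the effect of continuing ropivacaine plus methylprednisolone from 24 to 48 h, followed by patient-controlled ropivacaine, compared with switching to saline at 24 h, in patients who all had 24 h of the combination first.

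Then make three wording changes:

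1. In the Abstract's Discussion, drop methylprednisolone from the drugs whose needed amount is to be quantified, or mark that part as not estimable.
2. In the Discussion's list of study purposes, replace the efficacy of topical methylprednisolone with that of the combined regimen.
3. In the closing paragraph, confine validation and device-dosage statements to the combined regimen as given, and say that the steroid's separate effect is not tested.

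Ropivacaine bolus use can still be reported for the device.

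The cost is a narrower claim. No arm, endpoint, sample size or test changes. The trial was still recruiting, with 46 enrolled at the time of the article, so this can be settled before results are read. Testing the steroid's own effect would need a comparison in which only the steroid differs. By the illustration above, that is a much larger undertaking than this trial and is better left to a separate study.
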